**3. Project Title**

A double-blind, randomized, placebo-controlled, trial designed to assess the antiviral efficacy of Chloroquine in adult patients hospitalized with dengue.

**Proposed start date:** May 2007.

**Introduction and rationale**

Dengue fever (DF) is the most common vector-borne viral disease of humans, with more than 100 million cases recorded each year in tropical and subtropical countries and an increasing incidence in more temperate regions. Over half of the world’s population live in areas at risk of infection. In its most serious forms, dengue haemorrhagic fever (DHF) and dengue shock syndrome (DSS), it is also a major cause of morbidity and mortality, particularly in Southeast Asia where it is the principle reason for paediatric admission to hospital during the rainy season. In VietNam over the past three years we have noted an increasing incidence in adults. Data from dengue protein crystallographic studies have revealed opportunities to intervene in the replication cycle of dengue viruses (DENV). The pH-dependent structural changes involving the fusion loop in the envelope protein are central to successful virion fusion with the endosomal membrane and release of infectious viral nucleic acid into the cytoplasm (1). Chloroquine, a safe and pharmacologically well-characterized drug, inhibits several viruses requiring a pH dependent step for cell entry (2)(3). The in vitro inhibitory concentration (IC50) for chloroquine against dengue viruses is ~5 M (Fig. 1 from Novartis Institute for Tropical Diseases, Singapore). Furthermore, chloroquine inhibits the normal proteolytic processing of certain dengue virus proteins thereby reducing the infectivity of the mature virions (4). Following a 3-day course of therapeutic oral doses of chloroquine (600mg base on days 1 and 2, then 300mg base on day), the peak drug concentration (Cmax) ranges from 0.1 to 0.3g/mL (~0.3-1M) in plasma and 1 to 1.2g/mL (3.2-3.8M) in whole blood. Chloroquine is extensively sequestered in the tissues. In animals, from 200 to 600 times the plasma concentration may be found in the liver, spleen, kidney, and lung (5, 6). In humans, the highest concentrations of approximately 100M were measured in the marrow, liver, spleen and leukocytes (7). These data suggest a therapeutic potential for chloroquine in dengue-infected patients since the Cmax in relevant organs is likely to exceed the IC50 value. This trial asks the question whether chloroquine, by its action on the acidification of the intracellular vacuole, reduces viral load in patients with dengue.

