**Study Aims**

To measure the antiviral efficacy of chloroquine in the treatment of dengue.

Primary endpoint

The primary endpoint is;

1. time to negative DENV NS1 antigenaemia in plasma
2. time to negative reverse transcriptase (RT)-PCR detection of viral RNA in plasma

For the purposes of the study, time to a negative NS1 or PCR will be the interval between starting treatment and the first time NS1 or PCR is negative and remains negative for two consecutive measurements.

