#### Observations and Investigations

A full history and clinical examination will be performed at study entry and every day during the inpatient period. All clinical data will be documented in the case record form. The following investigations will be performed;

1. Chest X-ray or ultrasound on day of defervescance.
2. Hct, white cell count/differential, platelet count, SGOT, SGPT daily
3. Twice daily viral culture from plasma for minimum 5 days
4. Twice daily quantitative viral PCR from plasma for minimum 5 days
5. Twice daily assessment of Dengue NS1 levels for minimum 5 days
6. Twice daily measurement of plasma concentrations of the pro-inflammatory cytokines TNF, IL-6, IL-1B, IL12, IL-8 and the anti-inflammatory, IL-10 for minimum 5 days
7. ELISPOT assays to quantitate DENV-specific T cell responses
8. Microarray and PCR investigations to measure the effect of chloroquine on host gene-expression responses during acute disease

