# **Analysis plan- primary endpoints**

Baseline variables at randomization will be compared between the 2 treatment groups and analysed using the Kruskal-Wallis test for continuous variables and the chi-square test (or Fisher’s exact test) for categorical variables. Only study subjects who have detectable NS1 antigenaemia or viraemia (detected by PCR) at the time of study entry will be analysed for the primary endpoint measures. The primary endpoints are time to negative DENV NS1 antigenaemia in plasma and time to negative reverse transcriptase (RT)-PCR detection of viral RNA in plasma. Comparison of Kaplan-Meier survival curves (representing proportion of cases NS1 or PCR positive) between treatment groups using log-rank test will be performed. Adjusted treatment effect will be estimated and independent predictors will be identified using Cox regression analysis with stepwise forward variable selection procedure.

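### The trial asks whether chloroquine lowers viral load, but no planned analysis compares viral load in all infected randomised patients

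*Protocol*

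**What the plan says.** - **Question.** Protocol, Introduction and rationale: the trial asks whether chloroquine, through its effect on vacuole acidification, "reduces viral load in patients with dengue". Study Aims gives the aim as "To measure the antiviral efficacy of chloroquine in the treatment of dengue".
- **Background mechanism.** The introduction also says that chloroquine affects viral protein processing, "thereby reducing the infectivity of the mature virions". This is rationale and not part of the question.
- **Primary endpoints.** Study Aims and Analysis plan- primary endpoints name "time to negative DENV NS1 antigenaemia in plasma" and "time to negative reverse transcriptase (RT)-PCR detection of viral RNA in plasma". They are compared by Kaplan-Meier curves and log-rank test in patients who are NS1- or PCR-positive at entry.
- **Secondary endpoints.** The two lists cover fever, cytokines, liver enzymes, platelets, adverse events, complications, T-cell responses and gene expression. None is an amount of virus.
- **Data collected.** Observations and Investigations has quantitative PCR and NS1 levels twice daily for at least five days, and also "Twice daily viral culture from plasma for minimum 5 days".
- **Where viral quantity returns.** Only in Subgroup analysis. Items 3 and 4 use entry viraemia and entry NS1 to define subgroups, with the primary outcome unchanged. Item 5 is a viral-load slope in subjects with four or more positive RT-PCR results in a row.

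**The concern.** A question about quantity is answered by the time at which a test crosses its detection limit. Dengue virus clears without treatment (the protocol assumes a 72 h median), so a drug could lower viraemia for several days and change the distribution of clearance times only modestly. The one analysis of quantity selects patients on results obtained after randomisation. A treated patient whose virus falls quickly may not have four positives in a row and then drops out of the comparison. The arms being compared are therefore no longer the arms that were randomised. A fall in viral load could be present in the assay data and still have no protected comparison to show it.

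**Working it through.** **1. The plan's own figure.** Inputs from Sample Size: medians 72 h and 36 h (hazard ratio 2), power 0.8, type I error 0.05 (two-sided assumed).

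- Freedman: (1.96 + 0.84)² × (2+1)²/(2−1)² = 7.85 × 9 = 70.6, so 71 events. The protocol states 72, so this reproduces.
- Schoenfeld: 4 × 7.85/(ln 2)² = 65.3, so 66 events.

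The 72, 138 and 220 in that section do not agree with one another (138/0.648 = 213), which is a separate matter.

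**2. Power of the time-to-negative comparison.** From 220 patients, expected events are 220×0.8×0.9×0.8 = 127 to 220×0.8×0.9×0.9 = 143. Schoenfeld power:

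| Hazard ratio | 72 events | 127–143 events |
|---|---|---|
| 1.25 | 0.16 | 0.24–0.27 |
| 1.5 | 0.41 | 0.63–0.68 |
| 2 | 0.84 | 0.97–0.99 |

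The design is secure for the effect it names and weak for moderate ones.

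**3. From viral load to clearance time.** The protocol gives no kinetics, so two sets are assumed, each with a linear log10 decline that reaches the limit at 72 h for an average control.

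- Set A: entry 7 log10/ml, limit 3 log10/ml. Slope (7−3)/72 = 0.0556 log10/h. A sustained 0.5 log10 fall moves clearance by 0.5/0.0556 = 9 h. A 36 h shift corresponds to 36×0.0556 = 2 log10, or 100-fold.
- Set B: entry 2.4 log10 above the limit, decline 0.8 log10/day = 0.0333 log10/h. A 0.5 log10 fall moves clearance by 15 h. A 36 h shift corresponds to 1.2 log10, about 16-fold.

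**4. Simulated power.** 12-hourly samples over five days. Clearance is the first of two consecutive negatives. Log-rank on time to negative PCR is compared with a baseline-adjusted comparison of mean log10 load.

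- Set A: 80 per arm, between-patient SD 1.2 log10, slope variation 0.45 on the log scale, assay SD 0.3. Ranges are over repeat runs.
- Set B: 79 per arm (220×0.8×0.9/2), entry SD 1, slope CV 35%, assay SD 0.3, simulated control median about 82 h.

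| Effect | Set | Log-rank | Mean log10 load |
|---|---|---|---|
| None | A, B | 0.05 | 0.05 |
| Sustained fall 0.5 log10 | A | 0.28–0.33 | 0.75–0.82 |
| Sustained fall 0.5 log10 | B | 0.50 | 0.98 |
| Sustained fall 0.3 log10 | B | 0.22 | 0.74 |
| Fall 0.75 log10, 12–60 h only | A | 0.06–0.11 | 0.78–0.79 |
| Fall 0.5 log10, to day 3 only | B | 0.11 | 0.92 |
| Decline 30% faster | A | 0.78–0.82 | 0.86–0.89 |
| Decline 15% / 25% / 40% faster | B | 0.31 / 0.57 / 0.93 | 0.39 / 0.70 / 0.97 |

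With 500–600 replicates per scenario the Monte Carlo standard error is at most √(0.25/500) = 0.022.

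In the transient case of set B the average median clearance time does move, from 3.43 to 2.88 days. The curves separate early and come back together by the end of follow-up, which is why the log-rank test gains little.

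**5. The planned slope (set B).** In controls, 87% have four positives in a row. In treated patients the share is 66–80% for transient falls of 0.8 to 0.3 log10. Slope power is 0.06–0.09 for transient falls, 0.53 for a sustained 0.5 log10 fall, and 0.48, 0.85 and 0.99 for declines 15%, 25% and 40% faster. So the slope is the most sensitive of the three to faster decline and close to blind to a transient fall, and in every case it compares sets that treatment has altered.

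**The case against.** Several counter-arguments have force.

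- **Time to negative PCR already measures antiviral effect.** It fits the stated aim, and it responds to viral load. That stands. For a faster decline, the shape nearest to shorter clearance, the gap is small, and for a decline twice as fast both analyses have power near 1.
- **The protocol sets its own threshold.** Sample Size says that effects smaller than a 36 h reduction are unlikely to matter clinically. That defends the size of the clearance-time effect in the primary endpoint. It does not settle whether viral load falls, which is the question in the introduction.
- **The magnitude rests on assumed kinetics.** This is true. The large gaps belong to the sustained and transient shapes, and the protocol does not say which shape it expects. Only RNA was simulated, not NS1.
- **Viral load is not ignored.** A reader might infer that the quantitative data go wholly unanalysed. The slope in Subgroup analysis contradicts that, and its entry rule would keep most infected patients. Its fault is that it selects on results obtained after randomisation.
- **Infectivity is background.** A reader might also infer that the trial asks about infectivity and that an effect on infectivity alone could never appear in RNA or NS1. The question sentence names viral load only. Less infectious virions could also mean fewer newly infected cells and so less RNA later. The culture point is therefore limited to an assay with no stated use.
- **Supportive summaries are often left to an SAP.** In part. But this protocol lists its own secondary and subgroup analyses, and within those lists the stated question has no comparison in all infected patients.

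**Conclusion.** The mismatch stands on the text: the question is viral load, the primary and secondary endpoints contain no amount of virus, and the only analysis of quantity is confined to a subset that treatment can alter. The practical loss depends on the shape of the effect. Under the two assumed sets of kinetics it is large for a sustained 0.5 log10 fall (0.28–0.50 against 0.75–0.98) and for a transient 0.5–0.75 log10 fall (0.06–0.11 against 0.78–0.92), and modest for faster decline. The full-set summary had the higher power than log-rank for every effect tabulated.

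The documents do not support saying that a real antiviral effect will be reported as null, nor that the primary endpoints are wrong. This is an inexpensive improvement to the secondary endpoints, not a defect that invalidates the trial.

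**What to change.** In Analysis plan- secondary endpoints, add one pre-specified endpoint in all patients PCR-positive at entry: time-averaged log10 plasma viral RNA (area under the curve) from first dose to 120 h. Compare the arms with adjustment for the entry value, and fix in advance the rule for values below the detection limit, so that patients stay in the analysis after they clear. The set is defined at entry, so the comparison keeps the randomisation.

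Report the endpoint as supportive. Leave the primary endpoints and the rule for concluding on them unchanged. Making a conclusion on efficacy depend on an added secondary endpoint would open a second route to a positive reading without multiplicity control.

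Give viral culture a stated analysis, or label it exploratory in Observations and Investigations.

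Cost: protocol wording and one more secondary endpoint to report. The samples and assays are already planned.

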**Study Aims**

To measure the antiviral efficacy of chloroquine in the treatment of dengue.

Primary endpoint

The primary endpoint is;

1. time to negative DENV NS1 antigenaemia in plasma
2. time to negative reverse transcriptase (RT)-PCR detection of viral RNA in plasma

For the purposes of the study, time to a negative NS1 or PCR will be the interval between starting treatment and the first time NS1 or PCR is negative and remains negative for two consecutive measurements.

#### Sample Size

The following assumptions were made in calculating the sample size for EF study:

1. The median time to NS1 and PCR clearance in dengue population with normal standard of care is 72 hours
2. Most (90%) of dengue patients admitted to the trial will be day 3 of illness
3. The average proportion of cases that are NS1 and/or PCR positive on day 3 is 80%
4. At the end of follow-up (5 days after study entry), 20% of cases will still be positive for NS1
5. 10% of patients lost to follow-up

Under these assumptions, the minimum number of NS1 or PCR clearance cases required to be able to detect a 36 hours reduction of median time in Chloroquine arm as compared to standard care arm with a power of 0.8 and type I error 0.05--equivalently a hazard ratio relating to NS1 clearance of 2—is 72. Therefore total number will be 138/{0.8*(1-0.1)*(1-0.1)} =220 or 110 patients in each arm. The effect size in this sample size calculation study is large, but can be justified on the basis that a smaller effect size is unlikely to be clinically significant.

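### The total of 220 does not follow from the stated 72 clearances, so the stated power (0.8) and hazard ratio (2) do not describe a trial of this size

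*Protocol*

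**What the plan says.** All of this is in the Sample Size section of the protocol.

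- **Target.** The control median is 72 hours and the trial is to "detect a 36 hours reduction of median time in Chloroquine arm as compared to standard care arm". The stated power is 0.8 and the stated type I error is 0.05. The required number of clearances is given as: "equivalently a hazard ratio relating to NS1 clearance of 2—is 72".
- **Assumptions 2 to 5.** These are the share admitted on illness day 3 ("Most (90%) of dengue patients admitted to the trial will be day 3 of illness"), 80% of day-3 cases positive for NS1 and/or PCR, 20% still NS1-positive at the end of follow-up on day 5, and 10% lost to follow-up.
- **Total.** "Therefore total number will be 138/{0.8*(1-0.1)*(1-0.1)} =220 or 110 patients in each arm".
- **Justification.** The effect size is acknowledged to be large and is defended on the ground that "a smaller effect size is unlikely to be clinically significant".

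Two other sections bear on the point. Under primary endpoints, the analysis plan restricts the analysis to patients with detectable NS1 or viraemia at entry. Patient selection admits anyone with symptoms for three days or less.

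**The concern.** The sentence giving the total opens as a consequence of the 72 clearances but does not use them. It divides 138, a figure that appears nowhere else in the document, and the quotient is printed incorrectly. A reader cannot get from 72 to 220 by any stated step.

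The protocol therefore gives ethics committees, monitors and later readers a power and a detectable effect that belong to a smaller trial. If the listed assumptions hold, considerably more patients are randomised than the stated target needs. The trial would also have good power for effects below the one the same paragraph treats as the threshold of clinical interest.

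**Working it through.** **Inputs (Sample Size section).** HR 2; power 0.8; type I error 0.05, taken as two-sided because that reproduces the 72; equal arms; 0.8 positive; 0.8 cleared by day 5 (1 − 0.2); 0.9 admitted on day 3; 0.9 retained (1 − 0.1).

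**1. The 72 clearances.**
- Freedman: (1.96 + 0.842)² × [(2 + 1)/(2 − 1)]² = 70.6, or 72 with equal arms.
- Schoenfeld: 4 × (1.96 + 0.842)² / (ln 2)² = 65.3.
- One-sided testing would give 56 or 52.

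The stated 72 is reproduced as a *total* number of clearances. The fault lies after this step.

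**2. The printed division.** 0.8 × 0.9 × 0.9 = 0.648, and 138/0.648 = 213.0, not 220. Equal arms would give 214. Whole randomisation blocks of 40 do not explain 220 either, since it is not a multiple of 40.

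**3. From 72 to a number of patients.**
- Using the three factors in the printed formula: 72/0.648 = 111.1.
- Using assumptions 2 to 5 once each: 72/(0.8 × 0.8 × 0.9 × 0.9) = 138.9.
- Leaving out the day-3 factor: 72/(0.8 × 0.8 × 0.9) = 125.

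None of these gives 220. The second is close to the unexplained 138.

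**4. Check of assumption 4.** With exponential times and medians of 72 h and 36 h, 31.5% and 9.9% are still positive at 120 h. The mean is 20.7%, which agrees with the 20% assumed.

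**5. What 220 patients deliver.** Power is Φ(√d × ln 2 / 2 − 1.96) by Schoenfeld and Φ(√d / 3 − 1.96) by Freedman, where d is the number of clearances. The HR with 80% power is exp(2 × 2.802/√d) by Schoenfeld, or (1 + k)/(1 − k) with k = 2.802/√d by Freedman.

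| Case | Clearances (d) | Power at HR 2 (Schoenfeld / Freedman) | HR with 80% power | Median from 72 h to |
|---|---|---|---|---|
| Day-3 factor kept: 220 × 0.8 × 0.8 × 0.9 × 0.9 | 114.0 | 0.959 / 0.945 | 1.69 / 1.71 | about 42–43 h |
| Day-3 factor not a loss: 220 × 0.8 × 0.8 × 0.9 | 126.7 | 0.974 / 0.963 | 1.65 / 1.66 | about 43–44 h |

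**6. Other meanings of 138.**
- If 138 is a required number of clearances, power at HR 2 is 0.983 / 0.975.
- If 138 is a number of evaluable patients, 138 × 0.8 = 110 clearances give 0.954 / 0.939.
- If 72 was mistaken for a per-arm figure, the total of 144 gives 0.986 / 0.979, and 144/0.648 = 222, which matches neither printed number.

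Under none of these is 220 the size for 80% power at HR 2.

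**The case against.** **Double inflation is not proved.** A reader might infer that 138 is certainly 72 inflated once and then inflated again. The protocol does not support that as fact. It never says what 138 is; 138.9 would normally be rounded up to 139 or 140; and a mis-copied figure, or one from another calculation, is possible. This stands: double inflation is a probable cause only. The conclusion does not depend on it, as step 6 shows.

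**213 against 220 is small.** It is about 3% and might be undeclared rounding up to 110 per arm. That is fair, but it is printed as an equality and should be corrected.

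**Significance for small effects is not peculiar to 220.** A reader might infer that only the oversized trial can reach significance for effects the protocol discounts. With exactly 72 clearances, p < 0.05 is already reached at an observed HR of exp(2 × 1.96/√72) = 1.59 (72 h to about 45 h, a reduction of about 27 h). With 127 clearances it is reached at about 1.42 (a reduction of about 21 h). The larger size moves this threshold but does not create it.

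**It does not follow that the trial should be cut to 125.** A reader might infer this too. The 80% positivity is for NS1 and/or PCR, while time to negative NS1 and time to negative PCR are separate primary endpoints, and positivity on one marker may be lower. The 20% still positive refers to NS1 only. As an illustration, suppose 60% are positive on one marker (an assumption; the protocol gives no figure) and leave out the day-3 factor. Then 125 patients give 125 × 0.6 × 0.8 × 0.9 = 54 clearances and about 72% power at HR 2 (Schoenfeld), while 220 give 95 clearances and about 92%.

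**The day-3 factor is defensible.** Patients entering on day 1 or 2 are eligible and are analysed if positive, so it is not strictly a loss. But the protocol gives no positivity rate for them, and leaving them out is a cautious planning choice. Both versions are therefore shown.

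**Conclusion.** The Sample Size paragraph is wrong as written. The 72 clearances are sound. The step from 72 to 220 rests on an undefined 138 and a division that gives 213. On the listed assumptions, 72 clearances need about 139 patients (125 without the day-3 factor), so 220 is 81 to 95 more than the stated target requires. With 220, about 114 to 127 clearances are expected, giving about 95–97% power at HR 2 and 80% power at HR about 1.65–1.71.

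These figures assume two-sided testing at 0.05, proportional hazards, exponential times for the conversion to medians, and the protocol's own positivity, clearance and retention rates. They may be too high for NS1 or PCR taken alone. The error does not affect type I error or the validity of the analysis, and on these assumptions the promised power is exceeded.

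**What to change.** Keep 220 and rewrite the paragraph:

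1. Define 138 or remove it.
2. Print one chain from clearances to patients, using each assumption once and naming it: 72/(0.8 × 0.8 × 0.9 × 0.9) = 139. State whether the day-3 factor is a loss or a safety margin (125 without it).
3. Correct the printed division, and state any rounding up as such.
4. State what 220 delivers: about 114 to 127 clearances, about 95–97% power at HR 2, and 80% power at HR about 1.65–1.71.
5. Note that these figures may be lower for each primary endpoint separately, and why.
6. Because the protocol regards smaller effects as unlikely to matter clinically, add that a significant result will be judged against the 36-hour target using the estimated effect and its confidence interval.

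The cost is protocol wording only: no extra patients, and no change to conduct or to the planned tests.

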**Patient selection:**

Patients will be eligible to be admitted to the study if they have suspected uncomplicated dengue and:

1. Are >14 years of age
2. They have a history of symptoms of 3 days or less.
3. They give fully informed consent.
4. No previous history of hypersensitivity to Chloroquine
5. They are not pregnant.
6. They are not G6PD deficient
7. They are not receiving therapy for other disorders

